#### Relevant concomitant care permitted or prohibited during the trial {11d}

n/a: A non-clinical sample is studied and no clinical intervention is provided. Previously completed training in transcultural psychotherapy will be collected as a control variable.

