#### Control variables

In the pre-training assessment, sociodemographic data are collected through 18 items. In addition to standard socio-demographic information (age, gender, nationality), participants are asked whether they would perceive themselves as having a migration background. They are further asked whether they speak more than two languages fluently and whether they do/did any volunteer work for refugees or migrants.

In addition, questions are asked about therapeutic practice: duration of psychotherapeutic activity, specialization (behavioral therapy, depth psychology, etc.), and workplace (own practice, clinic, research institution, etc.). Finally, participants are asked whether, and if so to what extent, training with a focus on “culture in psychotherapy” has ever been completed.

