### Participant timeline {13}

Via a link, participants can access the detailed description and the inclusion criteria of the study online. After accepting the informed consent, the participants will be forwarded to the pre-training assessment (t0). During the pre-training assessment, the control variables as well as the primary (Multicultural Counseling Inventory and OnTracc) and secondary outcomes are measured. The participants will subsequently be randomized. The TG will directly start with the training. After the training (t1) and 2 (t4) and 6 months later (t5), the assessments are carried out again. The WG will complete a control assessment (t1) after the training group has completed the training. They will also complete the 2-month follow-up assessment (t2). After the 2-month follow-up assessment, they will start the training. After the training (t3) and 2 (t4) and 6 months (t5) later, they will complete the assessments. For the participant timeline, please refer to Fig. 1.

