### Sample size {14}

To the authors' knowledge, there are no web-based training programs for transcultural competence in Germany. For this reason, a concise estimate of the expected effect size is difficult to provide. A systematic review from 2020 on the effectiveness of cultural competence with nine studies showed effect sizes from small (*d* = 0.10) to large (*d* = 2.11) [63]. An online intervention to increase transcultural competence in the USA revealed medium effect sizes for the dimension attitudes and skills and large effect sizes for the dimension knowledge [40]. Based on the mixed results, we opted for a medium effect size.

A calculation with the Shiny App [64] with an effect size of *Glass’ delta* = 0.5 showed that a linear mixed model 3 (measurement time: pre, post, follow-up 1) × 2 (groups: training group vs. waitlist control group) requires a sample number of *N* = 174 (*α* = 0.05, power = 0.95).

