## Data collection and management

### Plans for assessment and collection of outcomes {18a}

All data will be collected online on the Unipark survey platform via participant self-report (https://www.unipark.com). The primary (transcultural competence) and secondary outcomes (experiences in treating patients with diverse cultural backgrounds) will be collected at each time point of measurement (pre, post, follow-up 1, follow-up 2). Control variables (sociodemographic information and therapeutic practice) will be assessed at baseline only. After training, satisfaction with the training (e.g., scope, practicability, formal design) will be assessed. For an overview of which questionnaires are applied at which time point, please refer to Fig. 1. For detailed information regarding the questionnaires, see {12}.

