## Statistical methods

### Statistical methods for primary and secondary outcomes {20a}

Outcomes will be evaluated using intention-to-treat (ITT) analysis. Group differences (group: training group vs. waitlist control group) in primary (transcultural competence; MCI and OnTracc) and secondary outcomes (experiences in treating people from other cultures) will be examined using piecewise linear mixed-effects models with repeated measures (time point: pre, post, follow-up 1). Likely will piecewise linear mixed-effects models be used to examine the longer-term effect of the training (including the four time points: pre, post, follow-up 1, and follow-up 2). The significance level will be set at *p* < .05.

Sociodemographic data will be listed by group condition and for the total group. Group comparisons will be examined at baseline to check for successful randomization. Categorical data are reported as *N* (%), continuous data as mean (SD).

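### Read in the ordinary way, the primary group-by-time model gives each arm its own baseline mean; a common baseline mean, or adjustment for the t0 score, would estimate the training effect more precisely from data already collected

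*Protocol article*

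**What the plan says.** Section {14} of the protocol article bases the sample size on "a linear mixed model 3 (measurement time: pre, post, follow-up 1") crossed with two groups: Glass' delta 0.5, α 0.05, power 0.95, N = 174. Section {20a} says that the outcomes "will be examined using piecewise linear mixed-effects models with repeated measures (time point: pre, post, follow-up 1"). In both places the pre score is a level of time, and so an outcome. The terms named are group and time point. No covariate is listed, and nothing is said about whether the arms share a baseline mean.

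Section {13} gives the order of events: consent, then the t0 assessment, then randomisation. It says that at t0 "the control variables as well as the primary (Multicultural Counseling Inventory and OnTracc) and secondary outcomes are measured". The baseline MCI and OnTracc scores are therefore outcomes measured at t0, separate from the control variables. Section {18a} defines the latter: "Control variables (sociodemographic information and therapeutic practice) will be assessed at baseline only".

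On prior training, section {11d} states: "Previously completed training in transcultural psychotherapy will be collected as a control variable". The Control variables section adds that "participants are asked whether, and if so to what extent, training with a focus on “culture in psychotherapy” has ever been completed". Section {20b} plans additional analyses of therapist characteristics, with practice duration and own migration background among its examples. Prior training is not among them.

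Section {20a} also says: "Group comparisons will be examined at baseline to check for successful randomization".

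**The concern.** A 3 × 2 layout, taken at face value, has six cell means, including a separate pre mean for each arm. With complete data, the training effect at a later time is then the difference between arms in mean change from pre. This is valid and unbiased, but it carries the full sampling error of the baseline difference, a difference that randomisation makes zero in expectation. A model with one baseline mean for both arms (five means), or with the t0 score as a covariate, removes the predictable part of that error.

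What is at stake is precision. The trial aims for 0.95 power, and section {14} mentions no allowance for dropout, so a larger standard error than necessary has a cost if the correlation over time is moderate.

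Two smaller points belong here. A variable labelled as a control has no named use in any analysis. And a check on whether randomisation succeeded, if done by significance test, would test a hypothesis already true by design.

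**Working it through.** **The plan's own figure.** With SD 1 and difference 0.5, the two-sample normal formula is n per arm = 2(z₁+z₂)²/0.25.
- One-sided α 0.05, power 0.95: 2(1.645+1.645)²/0.25 = 86.6, so 87 per arm and N = 174.
- Two-sided: 2(1.960+1.645)²/0.25 = 103.96, so 104 per arm and N = 208.

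The one-sided formula gives 174 exactly. However, a two-sided 174 also follows from a correlation: 87/103.96 = 0.837, which is 2(1−ρ) at ρ ≈ 0.58 (change score) or 1−ρ² at ρ ≈ 0.40 (baseline-adjusted). The article states neither sidedness nor the correlation entered in the app, so the figure does not show which calculation was made.

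**Inputs for the comparison.** From the article: 1:1 allocation and N = 174 (87 per arm), difference 0.5, α 0.05, pre measured before randomisation. Assumed: two-sided test, SD 1 at every time in both arms, equal correlation ρ between times, no dropout, and a piecewise model that fits the three time means freely.

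**Formulas.** The variance of the training contrast at one later time is (2/87)·v.
- Free baseline means: v = 2(1−ρ).
- Common baseline mean, or t0 as covariate: v = 1−ρ².
- Ratio: (1−ρ²)/[2(1−ρ)] = (1+ρ)/2, so the saving is (1−ρ)/2.

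Power is Φ(0.5/SE − 1.96), with SE = √(2v/87). For example, at ρ = 0.5:
- Free: v = 1.00, SE = 0.1516, power Φ(3.298−1.96) = 0.910.
- Common: v = 0.75, SE = 0.1313, power Φ(3.808−1.96) = 0.968.

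The N for 0.95 power is twice 103.96·v rounded up.

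| ρ (assumed) | v free | v common | ratio | power at 174, free | power at 174, common | N for 0.95, free | N for 0.95, common |
|---|---|---|---|---|---|---|---|
| 0.3 | 1.40 | 0.91 | 0.65 | 0.796 | 0.933 | 292 | 190 |
| 0.5 | 1.00 | 0.75 | 0.75 | 0.910 | 0.968 | 208 | 156 |
| 0.6 | 0.80 | 0.64 | 0.80 | 0.958 | 0.985 | 168 | 134 |
| 0.7 | 0.60 | 0.51 | 0.85 | 0.989 | 0.996 | 126 | 108 |
| 0.9 | 0.20 | 0.19 | 0.95 | 1.000 | 1.000 | 42 | 40 |

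Generalised least squares on three time points with equal correlations gives the same ratios for the post contrast at ρ 0.3, 0.5 and 0.7. For the average of post and follow-up 1 the ratios are lower: 0.533, 0.667 and 0.80. Below ρ = 0.5 the change contrast is less precise than one that ignores baseline altogether (v = 1, power 0.910).

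**Prior training.** Suppose it correlates r with both the baseline and the later score. The further share of variance removed once baseline is in the model is r²(1−ρ)²/[(1−r²)(1−ρ²)]. The smallest value over r 0.2 to 0.4 and ρ 0.5 to 0.7 is 0.7% (r 0.2, ρ 0.7) and the largest 6.4% (r 0.4, ρ 0.5). Both correlations are assumed.

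**The case against.** The strongest reply is that free baseline means appear nowhere in the text. The article gives no equation, and parameterisation is commonly left to an analysis plan that is not shown. If the model has no group term at pre, the proposed change is already in place. This stands: the point is conditional on the ordinary reading. It is still worth making, because the article fixes the structure (pre as a repeated outcome, 3 × 2) and that structure, left unqualified, leads to the less precise contrast.

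A second reply is that the size depends on ρ, which the document does not give. This also stands. At ρ = 0.6 the free-baseline model already reaches 0.958, and at 0.8 or above little is gained.

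Several stronger readings are tempting but not supported:
- A reader might infer that baseline scores are collected as control variables and then left unused. Sections {13} and {18a} keep them apart from the control variables, and they enter the model as the pre measure.
- A reader might infer that all the collected characteristics go unused. Section {20b} gives practice duration and migration background a role; only prior training has no named analysis.
- A reader might infer that the baseline comparison will drive post-hoc adjustment. Section {20a} names no significance test and plans no adjustment triggered by imbalance.

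**Conclusion.** The concern holds as a point of efficiency and clarity. If the baseline means are left free, constraining them or adjusting for the t0 score cuts the variance of the training contrast by (1−ρ)/2. In large samples this is never less precise, and at 87 per arm the cost of estimating one slope is negligible. The gain is material at ρ of about 0.3 to 0.5, modest at 0.6 to 0.7 and small at 0.9. If the means are already constrained, it is zero.

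The figures rest on assumed ρ, equal SDs, a two-sided test and no dropout. They do not show bias in the planned model. Nor do they show that the trial misses its 0.95 target: at ρ of about 0.58 or more, a two-sided change-score analysis reaches it with 174 complete cases. Adding prior training is not needed for precision; the article should only make its label consistent with its use.

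**What to change.** In section {20a}, state either that the arms share one baseline mean (no group effect at pre, with group effects at post and follow-up 1), or that the t0 score of the same scale enters as a covariate with post and follow-up 1 as the outcomes. The first keeps pre as a repeated measure and so stays closest to the present text.

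Two minor edits: present the baseline comparison as a descriptive table by arm without tests, and say in section {11d} or {20a} how prior transcultural training is used, or drop the control-variable label.

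The cost is analysis wording only. All the data are already collected at t0, and neither the sample size nor the assessment schedule changes. The wording should be settled before outcome data are analysed.

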#### Provisions for post-trial care {30}

n/a: There is no anticipated harm and compensation for trial participation apart from a certificate of attendance. For this reason, there will be no need to provide post-trial care. Nevertheless, participants can reach out to the study management via email or telephone at any time if needed.

### Outcomes {12}

#### Primary outcome measures

The primary outcome is transcultural competence. Transcultural competence will be assessed at the beginning of the training, at the end of the training, and at the 2- and 6-month follow-up (see Fig. 1). For this purpose, the well-validated Multicultural Counseling Inventory (MCI) [44], translated into German by [name] [22], is used. The MCI captures general transcultural competence as conceptualized by Sue et al. [34]. With a total of 40 items, transcultural competence is assessed on the subscales *skills* (11 items, e.g., “I am able to quickly recognize and recover from cultural mistakes or misunderstandings.”), *cultural self-awareness and other-awareness* (10 items, e.g., “In order to be able to work with minority clients, I frequently seek consultation with multicultural experts and attend multicultural workshops or training sessions.”), and knowledge (11 items, e.g., “I use innovative concepts and treatment methods.”). In an additional fourth subscale, *therapeutic relationship* is assessed (8 items, e.g., “I am confident that my conceptualizations of client problems do not consist of stereotypes and biases.”). The MCI allows to compute both a total score and scores for the four subcategories. The 40 self-report items are answered on a 4-point Likert scale ranging from 1 (very inaccurate) to 4 (very accurate). Research indicates that the MCI is a suitable psychometrically robust instrument for evaluating transcultural competence in multicultural training processes [61]. The dimensions appeared to be distinct yet interrelated [61]. Internal consistency reliabilities (Cronbach’s alpha) ranged from .67 to .81 in the subscales and .86 for the full scale [44].

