After each module, participants receive written feedback from a supervisor about the completed exercises and upcoming questions. The supervisors are at least bachelor-level clinical psychologists and receive regular supervision from an experienced clinical psychologist. The feedback is composed of prefabricated text templates and individualized to the participants’ responses. In the feedback, participants are complimented on their engagement; then, they receive individual feedback on the exercises they have completed. If they have noted specific questions in the module, these are also answered by the supervisor. The supervisor further encourages participants to keep up their active participation. Through sending the feedback, the next module will be unlocked. Participants are accompanied throughout the training and have the opportunity to contact the supervisors.

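### One item of the MCI awareness subscale asks about attending multicultural training, so allocation alone can raise that subscale; a sensitivity analysis without the item would settle it

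*Protocol article*

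**What the plan says.** Under Primary outcome measures, the protocol article measures transcultural competence with the MCI and, as a second questionnaire, OnTracc. On the MCI it says: "With a total of 40 items, transcultural competence is assessed on the subscales" skills, awareness and knowledge, plus a fourth subscale for the therapeutic relationship. Awareness has 10 items, and the example given for it is "In order to be able to work with minority clients, I frequently seek consultation with multicultural experts and attend multicultural workshops or training sessions". Items are scored 1 to 4. On scoring: "The MCI allows to compute both a total score and scores for the four subcategories". The end of the Background section names knowledge, skills and awareness as primary outcomes, so the awareness score carries a primary claim.

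The intervention is a six-module transcultural training with written supervisor feedback after every module. Of the supervisors, the Didactics section adds: "Participants are accompanied throughout the training and have the opportunity to contact the supervisors".

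On timing, the Participant timeline states: "The WG will complete a control assessment (t1) after the training group has completed the training". The waitlist arm begins training only after its 2-month follow-up assessment. The main between-arm model in Statistical methods {20a} uses the pre, post and follow-up 1 time points.

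**The concern.** The item asks about behaviour that the trial itself supplies to one arm. By the post assessment, a training-arm member has been offered six weeks of multicultural training with individual feedback. The waitlist arm has not been given it at either between-arm comparison. An honest answer can therefore move up in one arm because of the randomised assignment, whether or not the person has become more competent.

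This differs from the biases listed under Limitations. Social desirability concerns answers that are inaccurate, and the waitlist caveat concerns a weak comparator. Here a perfectly accurate answer produces the difference. The reliability figures and the cited suitability of the MCI for evaluating training do not address it either, because internal consistency does not show that an item is independent of allocation.

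At stake is the reading of an MCI awareness effect: part of it could restate who was assigned to training.

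**Working it through.** **The plan's own figure.** Sample size {14} gives N = 174 for Glass' delta 0.5, alpha 0.05 and power 0.95. A normal approximation for two means gives:

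- one-sided: 2 × (1.645 + 1.645)² / 0.5² = 86.6, so 87 per arm and N = 174;
- two-sided: 2 × (1.960 + 1.645)² / 0.5² = 104.0, so 104 per arm and N = 208. Baseline adjustment with a correlation of about 0.40 brings this to 174, since 208 × (1 − 0.404²) ≈ 174.

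The figure can be reached, though the article does not identify the route. It is not disputed here. It supplies the benchmark (0.5 SD) and the arm size (87).

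**Item weight (from the document).** In a mean score, one item counts 1/10 of awareness and 1/40 of the total.

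**Assumptions (not in the document).** Mean-score SD of 0.4 to 0.5 for awareness and 0.3 for the total. Mean rise on the item due to allocation alone: 0.5 to 1 point.

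**Formula.** Shift in SD units = (item rise × item weight) / SD.

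| Rise on item | Awareness | Total |
|---|---|---|
| 0.5 point | 0.05 / 0.5 to 0.05 / 0.4 = 0.10 to 0.125 | 0.0125 / 0.3 = 0.04 |
| 1 point | 0.10 / 0.5 to 0.10 / 0.4 = 0.20 to 0.25 | 0.025 / 0.3 = 0.08 |

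Against the planned 0.5, that is 20% to 50% on awareness and about 8% to 17% on the total.

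**Cross-check by a second route.** The protocol reports that alpha "ranged from .67 to .81 in the subscales and .86 for the full scale". For k items with item SD s:

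- mean inter-item correlation r = alpha / (k − alpha(k − 1));
- SD of the sum score = s × √(k(1 + (k − 1)r)).

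With s assumed between 0.6 and 0.9:

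- Total (k = 40, alpha .86): r = 0.86 / (40 − 33.54) = 0.133; SD of the sum 9.44 to 14.16, or 0.24 to 0.35 as a mean score.
- Awareness (k = 10, alpha .67 to .81): r = 0.169 to 0.299; SD of the sum 3.01 to 5.47, or 0.30 to 0.55 as a mean score.

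The assumed SDs lie inside these ranges. By this route a half-point rise gives 0.09 to 0.17 SD on awareness and 0.04 to 0.05 SD on the total. A 1-point rise gives 0.18 to 0.33 SD and 0.07 to 0.11 SD.

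**Chance that the artefact alone is significant.** Simple two-sided comparison at 0.05, 87 per arm, SE = √(2/87) = 0.152 SD, no true effect:

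- awareness: 10% at 0.10 SD, rising to 38% at 0.25 SD;
- total: about 6% at 0.04 SD and 8% at 0.08 SD.

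The nominal rate is 5%. These are guides only, because the planned analysis is a mixed model.

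**The case against.** The strongest reply is that the shift may be small.

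- **Wording.** The item says *frequently* and joins two behaviours, consulting experts and attending training. One six-week course need not count as frequent. Feedback partly built from text templates, by supervisors whose minimum level is a bachelor's degree, is not clearly expert consultation that the participant sought out.
- **Plausible size.** With an item SD of 0.6 to 0.9, a 1-point mean rise is 1.1 to 1.7 item SDs, which is large. Under intention to treat, some of the training arm will not have finished the modules.
- **Second measure.** OnTracc has its own 10-item awareness factor, and none of its quoted example items asks about attending training.
- **Scale and plan.** Using a published scale intact is defensible, and an item-deleted score could sit in an analysis plan that is not shown.

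All of this stands as a limit on size. None of it removes the mechanism or its direction.

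A reader might go further and infer that, for this item, intervention and outcome are the same thing, or that the MCI result as a whole is an artefact of allocation. The document does not support either. Only part of a two-part item overlaps with the training, and the effect on the total is small under every assumption above. Nor can it be said that other MCI items share the problem, because the full item list is not shown.

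**Conclusion.** The point holds in a limited form. One of the 10 awareness items can rise through allocation alone at both between-arm comparisons, in the direction that favours the training. The overlap is not named in the protocol; the general caveat about self-report does not cover it.

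Under the stated assumptions the bias is about 0.10 to 0.25 SD on awareness and 0.04 to 0.08 SD on the total. The first is material against a planned 0.5; the second is not. Only the item weights come from the document. The SDs and the 0.5 to 1 point rise are assumptions, and the true rise could be smaller. The planned full-scale analysis remains legitimate. What needs protection is the interpretation of an MCI awareness effect.

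**What to change.** Keep the full validated MCI score as planned. Prespecify, before the data are analysed, a sensitivity analysis that recomputes MCI awareness (9 items) and the MCI total (39 items) without this item and compares the arms at the post assessment and the 2-month follow-up. Report both versions. Interpret an MCI awareness effect as a gain in competence only if it holds without the item, and read it alongside the OnTracc awareness result.

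Do not add an instruction telling respondents to leave out the study training. Recruitment began in April 2023, so a change now would make the instrument differ between participants and between one participant's own assessments.

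The cost is one rescoring and one rerun on data collected anyway. The downside is that the shortened score departs slightly from the published scale, which is why both versions must be shown.
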